## Abstract

**Introduction:**

Caesarean birth (CB) under neuraxial anaesthesia (NA) is the most performed inpatient operation in the UK. The incidence of intraoperative pain during caesarean delivery performed under neuraxial anaesthesia is unclear, with limited data that used patient-reported measures to investigate intraoperative pain. The short- and medium-term impacts on patients of this adverse event are unknown.

**Methods and analysis:**

We will undertake a multicentre, prospective observational cohort study to evaluate the incidence and impact of pain experienced by patients during CB performed under neuraxial anaesthesia. Routine audit data will be collected for all patients undergoing caesarean delivery for any indication during a 1 week window at participating hospitals within the UK and Queensland, Australia. The dataset will include patient, anaesthetic, obstetric and neonatal risk factors for intraoperative pain. Local investigators will then seek informed consent from patients either before or within 24 hours of delivery to record patient experience and patient-reported outcomes at 24 hours and 6 weeks postdelivery. Local investigators at participating hospitals will also complete a survey evaluating compliance with evidence-based structural standards at their sites. The patient characteristics, structures, processes and outcomes will be described. Inferential techniques will be used to evaluate the relationship between risk factors and postoperative outcomes.

**Ethics and dissemination:**

This study received ethical approval from the Leicester Health Research Authority and Care Research Wales, REC reference 24/EM/0084) on 24 May 24. The study received ethical approval from the Human Research Ethics Committee of Metro North Health in Australia on 25 March 2024 (REC Ref HREC/2024/MNHA/103767). The results of the study will be reported in accordance with the Strengthening the Reporting of Observational Studies in Epidemiology statement. The results will be disseminated via conference presentations, peer-reviewed academic journals and reports prepared for patients, the public and policy makers.

**Trial registration number:**

ISRCTN15269213.

STRENGTHS AND LIMITATIONS OF THIS STUDYThis comprehensive study aims to recruit patients from across the UK and Australia.This study uses patient-centric outcome measures and patient-reported data for its primary and secondary outcomes.This study focuses on an important patient concern and aims to investigate how this may impact 6-week postpartum recovery.The snapshot nature of the study means that system pressures identified may not be generalisable.Those patients most affected by the primary outcome may choose not to participate in the study.

## Introduction

 Caesarean birth (CB) is the most performed inpatient surgical procedure worldwide.^1^ The CB rate is rising in most countries. In the UK, over 136 000 patients between March 2023 and 2024 were delivered by this mode, representing 42% of all deliveries.^2^ Neuraxial anaesthesia techniques are associated with lower neonatal and maternal morbidity^3^ and are considered to be the gold standard anaesthesia for CB.^4^ These techniques are preferable to general anaesthesia as they are associated with lower rates of neonatal and maternal morbidity, while promoting improved maternal–infant bonding, earlier breastfeeding, partner presence during surgery and superior postpartum recovery.^5^ However, the effectiveness of neuraxial anaesthesia is not absolute, with failure rates and intraoperative pain incidence varying widely due to a complex interplay of patient-specific factors, clinician experience, anaesthetic technique, obstetric conditions, neonatal conditions and institutional protocols.^6^ Furthermore, there is a lack of consistency in the literature on how intraoperative pain during CB should be measured and managed, and for this reason, the true incidence of intraoperative pain remains unclear. Published data on the incidence of pain during CB are predominantly from single centre studies, with incidence rates ranging widely from 1.7%^7^ to 33%.^8^,^10^ A systematic review of randomised controlled trials in patients having a scheduled CB reported the overall incidence of pain, defined as requirement for unplanned supplemental analgesia, repeat neuraxial technique or conversion to general anaesthesia, as 14.6%.^11^

Current guidance emphasises the risk of adverse psychological sequelae as a result of pain during CB and provides expert recommendations on its management; however, the scale of the potential impact of intraoperative pain experienced on short- and medium-term on the patient remains insufficiently explored.^6^ There have been no prospective studies evaluating neuraxial anaesthesia from the patient’s perspective, how intraoperative pain is managed, and what the outcomes are for those that experience this adverse event.

Few studies in the past decade have evaluated pain during CB using contemporary obstetric anaesthesia practices and techniques. During this time, there have been changes to both anaesthetic and obstetric staffing levels within obstetric units in the UK. Advances in labour ward epidural analgesia include the use of changes to practices in ‘topping-up’ epidurals, increased use of lower concentration epidural local anaesthetic for labour analgesia, addition of techniques into clinical practice to initiate and maintain labour analgesia and surgical anaesthesia, including combined spinal epidural or dural puncture epidural and developments in labour analgesia delivery strategies and epidural pump technology. This is particularly relevant as labour epidural analgesia is frequently converted to surgical anaesthesia for intrapartum CB.

Therefore, we plan to conduct an international prospective, observational cohort study to address this knowledge gap. The aims of the study are to elucidate the incidence, risk factors and sequelae of pain experienced during CB performed under neuraxial anaesthesia; and to use patient-reported outcome measures (PROMs) to evaluate the physical and psychological impact on those who experience intraoperative pain.

## Methods

### Key study dates

The study opened for data collection to national sites on 17 March 2025 and closed to new patient recruitment on 17 May 2025. We expect all data collection to be complete by 1 August 2025.

### Study design

Snapshot Obstetric National Anaesthetic Research Project (SONAR1) is a prospective, multicentre, observational cohort study. The study has two components:

Patient study: cohort study of patients undergoing CB under neuraxial anaesthesia in participating hospitalsOrganisational survey: study of institutional and structural risk factors that may influence incidence and/or outcomes for patients during CB.

A pilot study has been completed at University College London Hospital, enabling us to refine and modify the study protocol and the final version to be delivered across the UK and Australia.

### Research questions

RQ1: What is the incidence of intraoperative pain reported by patients during CB performed with neuraxial anaesthesia?

RQ2 What is the incidence of incidence of intraoperative pain reported by clinicians during CB performed with neuraxial anaesthesia?

RQ3: What are the hospital-, patient-, clinician-, anaesthetic- and obstetric-related factors associated with the incidence of pain during CB performed under neuraxial anaesthesia?

RQ4: What are the hospital-, clinician-, patient-, anaesthetic- and obstetric-related factors associated with the short- and longer-term outcomes following CB performed under neuraxial anaesthesia?

### Objectives

To estimate the incidence of patient and clinician-reported intraoperative pain during CB conducted with neuraxial anaesthesia. (RQ1)

To describe how intraoperative pain is managed, and to describe how successful practice strategies are. (RQ2,3)

To evaluate day 1 and 6-week patient reported outcomes related to intraoperative pain during CB (RQ1,2,3)

To evaluate the physical and psychological impact on patients of CB in the short- and medium-term using PROMs. (RQ 2,3)

## Eligibility criteria

### Hospital level

All hospitals within the United Kingdom’s National Health Service (NHS) and Australian public hospitals with a consultant-led obstetric unit and anaesthetic support are eligible to take part.

On completion of a site initiation visit, local principal investigators (PI) will be provided with access to an online organisational survey. They will be asked to complete this in conjunction with the institutions’ clinical lead for obstetric anaesthesia. The survey explores the preoperative, intraoperative, postoperative and structural factors that may influence the incidence or impact of intraoperative pain during CB. The information will be used to examine hospital and structural risk factors that may impact the incidence, management and follow-up of intraoperative pain.^6 12^

### Patient level

#### Inclusion criteria

Patients who are 18 years or overUndergoing a CB that is scheduled or unscheduled of any urgency category≥32 weeks’ gestationNeuraxial anaesthesia is the planned primary mode of anaesthesia.

#### Exclusion criteria

Patient refusalOther modes of birth or obstetric surgical procedures, such as instrumental delivery, are not eligibleCB where a general anaesthetic is planned as the primary mode of anaesthesiaNeonatal or fetal demise

### Consent

As early as possible following admission to a participating maternity unit, all potential participants who meet the inclusion criteria will, wherever possible, be provided with information about the study via a participant information sheet (PIS). Any member of the clinical or research staff can give the participant a patient informational sheet and inform them that the study is occurring within the facility, but any specific participant questions regarding the study should be directed to a local investigator. In most cases, provision of information regarding SONAR1 will be provided shortly following admission and before delivery. However, in emergencies or for other local logistical reasons, some participants may only receive the patient information sheet following delivery. In this case, local investigators are required to ensure that the participant is given at least 1 hour to consider the information on the patient information sheet before being approached to consent.

Patients who meet the inclusion criteria will be approached to provide informed consent to participate at the earliest feasible opportunity postoperatively during inpatient hospitalisation. Consent can be sought by anyone who has completed the required training to obtain consent according to local guidelines—this may include; clinical staff, research nurses, research midwives or non-clinical research assistants. If participants are too unwell to be approached during the immediate postoperative period, local investigators should use their judgement about the appropriate timing to approach for consent. For patients who are admitted to high dependency or intensive care postpartum, local investigators should use their clinical judgement as to whether a patient can be approached to participate. This process is summarised by figure 1, demonstrating the planned flow chart for each eligible patient.

**Figure 1 F1:**
[figure not shown]
Flow chart for eligible patient. CRF, case record form; PIS, participant information sheet; REDCap, Research Electronic Data Capture; SONAR1, Snapshot Obstetric National Anaesthetic Research Project; ASAP, as soon as possible; DEL, delivery.

## Data collection and follow-up procedures: summary

Data will be collected by local investigators using three case record forms (CRFs). CRF1 does not require patient consent and consists of routine patient, obstetric and anaesthetic audit data that are collected during the CB. It is completed by the attending anaesthetist present for the CB for all patients. Patients who provide informed consent to participation in the study will be approached to complete CRF 2 within 24 (±6 hours) of surgery. Finally, at 6 weeks (±3 days) following delivery, consenting participants will be contacted by local investigators by telephone, to complete CRF3.

### Case record forms

All case record forms discussed here are available in online supplemental file 1.

Perioperative anaesthetists will complete CRF 1 for every patient during the study period. If perioperative anaesthetists are unable to fully complete the CRF1 at the time of surgery, local investigators can complete the CRF1 retrospectively, through accessing patient records.

Eligible patients will be asked to complete CRF2 with local study investigators within 24 (±6) hours of their delivery. CRF2 includes a previously described and validated PROM: the Maternal Satisfaction Score^13^ and additional questions to evaluate intraoperative experience and satisfaction with anaesthesia and analgesia during their delivery. Patients will also be asked to provide their contact details to allow local investigators to contact them at 6 weeks (±3 days) for the purpose of completing *CRF3* (detailed below). Patients may have visits from family and other healthcare workers at this time; therefore, it is acceptable to return for more than one visit. Predetermined data collection visit times are encouraged, if within the data collection timeframe and investigator resources allow. The study documents are available in the six most commonly spoken languages in patients who do not speak English, and Welsh. Local investigators should attempt to make it possible, using their local interpretative services to ensure patients who do not speak English are able to take part, if they wish. The patients will need to be able to complete CRF2 with an investigator.

CRF3—This CRF will be used to collect follow-up data at 6 weeks (±3 days) from participants who provide consent. The PROMs used will be the validated Edinburgh Postnatal Depression Scale (EPDS), the Post-Traumatic Stress Disorder (PTSD) Checklist for *DSM-5* (PCL-5) and Generalised Anxiety Disorder- 7 Scale (GAD7). In addition, the patient will be asked regarding pain at rest and on movement. Patient follow-up will be conducted over the telephone by local investigators. A maximum of three attempts will be made to contact participants, with each attempt being noted on the study log. If no follow-up is completed after three attempts, no further attempts will be made, and the participant should be deemed ‘lost to follow-up’. This should be recorded as such on the study log. If contact is made, but the participant asks to be called back later, it is acceptable to make more than three phone calls. If contact with the participant is made, but *CRF3* is only partially completed (eg, due to other time commitments), it is acceptable to make more than three attempts to recontact; however, recontact should be done with sensible judgement—local investigators should be dissuaded from an excessive number of attempts which could be deemed to be too intrusive by consenting participants. If the patient’s first language is not English and they have consented, they are able to complete CRF3 via telephone using telephone translation services locally. This process is summarised in figure 2, which demonstrates the methodology of data collection for each patient.

**Figure 2 F2:**
[figure not shown]
Flow chart of methodology for data collection and follow-up procedures. CRF, case record form; PIS, participant information sheet; REDCap, Research Electronic Data Capture; DEL, delivery.

In the event of a participating patient scoring >11 for EPDS, 30 for PCL-5 or >10 for GAD-7, the participant should be informed that her score would suggest she has screened positively for postnatal depression, PTSD or anxiety, respectively. The participant should be encouraged to see their general practitioner (GP) or health visitor as soon as possible. If the patient reported suicidal ideation (Q.10 of EPDS), they should be advised to seek immediate medical help, for example, emergency department (ED) visit. Local investigators should offer a letter that details resources available to the patient to support their mental health. If the patient consents, a letter will also be sent to their GP explaining the study and that the patient has been flagged as at risk of either postnatal depression, PTSD or anxiety. If a patient responds with anything other than ‘Never’ for EPDS question 10 regarding self-harm, or if the investigator has concerns regarding their safety or that of the participant’s family, then as well as the letters of resources, the local health visitor teams or local maternity safeguarding teams should be informed. The patient should be advised to visit their GP, contact their health visitors or attend local EDs if appropriate. Local investigators should also contact their local hospital maternity safeguarding team according to local protocols if they have any concerns arising from their interaction with study participants.

### Organisational survey

No follow-up for the organisational survey will be required.

### Outcome measures

Our primary outcome will be the incidence of intraoperative pain as reported by patients in CRF2. Our secondary outcomes will include the incidence of physician-reported pain, incidence of depression, anxiety and/or PTSD from screening at 6 weeks (± 3 days), and pain scores at both 24 hours (±6 hours) and 6 weeks (±3 days). Maternal Comfort and Maternal Satisfaction Scores at 24 hours (±6 hours) will also be secondary outcome measures. A further secondary outcome will be to describe the current practice of how intraoperative pain is managed.

## Analysis plan

### Descriptive statistics

The descriptive epidemiology of the patient, hospital, clinician obstetric and anaesthetic data collected in CRF1 will be reported. Frequency and row percentages will be presented for categorical and binary variables, while median and (IQRs) interquartile ranges will be provided for continuous variables. We will report the incidence of pain during CB (from both patient and clinician perspectives) and how this was managed.

### Inferential statistics

Inferential statistics will be used to understand modifiable and non-modifiable risk factors for pain during CB and self-reported outcomes measured. This analysis will also enable us to explore the relationships between patient and structural risk factors, care processes, short-term and longer-term outcomes. This will include regression modelling to determine factors associated with intraoperative pain, including patient, anaesthetic and obstetric risk factors, and institutional and country level structural and process indicators. Where appropriate, we will use multilevel multivariable regression to investigate these relationships and account for hospital-level clustering.

The results of the study will be reported in accordance with the Strengthening the Reporting of Observational Studies in Epidemiology (STROBE) statement.^14^

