### Conclusions

SONAR1 will use a multi-centred prospective study design and PROMs to obtain detailed information from a comprehensive sample of patients having a CB in the UK and Australia to investigate the incidence of intraoperative pain, neuraxial failure and the impact on short and medium-term outcomes for patients.

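### With only two countries, no country-level structural or process indicator can be told apart from the UK–Australia contrast itself

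*Protocol article*

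**What the plan says.** The Analysis plan, under Inferential statistics, says that regression will identify what is associated with intraoperative pain. Besides patient, anaesthetic and obstetric risk factors, it names "institutional and country level structural and process indicators". The only model structure given is, where appropriate, "multilevel multivariable regression to investigate these relationships and account for hospital-level clustering". No country level of the model is described and no country-level variable is named.

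The sites are described in four places:
- Abstract, Methods and analysis: "participating hospitals within the UK and Queensland, Australia".
- Strengths and limitations: the study "aims to recruit patients from across the UK and Australia".
- Hospital level, under Eligibility criteria: NHS hospitals in the UK "and Australian public hospitals with a consultant-led obstetric unit and anaesthetic support are eligible to take part".
- Conclusions: "a comprehensive sample of patients having a CB in the UK and Australia".

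No section mentions a third country, and none treats the nations of the UK as separate units.

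**The concern.** A country-level indicator has one value per country. Regression can learn about it only by comparing countries, and here there is a single comparison to make. Whatever differs between the UK and the Australian sites, measured or not, sits in that one comparison. A coefficient printed against a named national structure or process would therefore carry all of those differences, and the data could not say which of them produced it.

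What is at stake is interpretation. Risk factors for pain are a stated aim, and the results are to go to policy makers, to professional colleges in both countries and to the chief executives of participating NHS organisations. If a UK–Queensland difference were presented to them as the effect of a national structure, it would claim more than the study can show.

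**Working it through.** The protocol gives no figure on this point to reproduce. The check is whether the planned terms can be estimated.

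**Inputs.** Two countries (abstract, strengths and limitations, eligibility, conclusions). Indicators at both hospital and country level, in the plural (Inferential statistics). For illustration, two hospital-level covariates and 100 hospitals; neither number comes from the protocol, and the result does not depend on them.

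**Step 1: one indicator.** Let C = 0 for the UK and 1 for Australia. An indicator Z that equals a in the UK and b in Australia is

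Z = a + (b − a) × C.

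Its correlation with C is therefore +1 or −1. In a model without C, the coefficient of Z is the country coefficient divided by (b − a). It is the same contrast on another scale.

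**Step 2: more than one indicator.** A second indicator W, equal to c in the UK and d in Australia, satisfies

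W = c + [(d − c)/(b − a)] × (Z − a).

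It is an exact function of the first, so the two cannot both be estimated.

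**Step 3: rank of the design matrix.** A model is estimable only if the rank equals the number of columns.

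| Terms (intercept and two hospital covariates in every model) | Columns | Rank |
|---|---|---|
| Country | 4 | 4 |
| Country + 1 country-level indicator | 5 | 4 |
| Country + 2 country-level indicators | 6 | 4 |
| No country term, 1 country-level indicator | 4 | 4 |
| No country term, 2 country-level indicators | 5 | 4 |

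The first row shows that hospital indicators plus one country term can be estimated. The fourth row also has full rank, but by Step 1 it is the first row with country renamed.

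**Step 4: the four UK nations counted separately.** This is an assumption that the protocol does not make. It gives 4 + 1 = 5 units and 5 − 1 = 4 between-country degrees of freedom. With country fixed effects, one country-level indicator already fails (rank 7 of 8). Without them, four indicators can be fitted (rank 7 of 7) and a fifth cannot (rank 7 of 8). Four indicators on four degrees of freedom saturate the between-country variation, so nothing is left to show that the indicators, and not the countries, explain it.

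**The case against.** The strongest reply is that one phrase is being read too hard. RQ3 and RQ4 ask about factors tied to the hospital, the patient, the clinician, the anaesthetic and the obstetric care, and do not mention country. The objectives do not mention it either. The only structural data source described is the organisational survey, completed site by site. A natural reading is hospital indicators plus a term for country, which is what is recommended below. This largely stands and is why the point is minor. It does not remove the point: the sentence names country-level indicators as factors for the regression, and rewording costs nothing if a single adjustment term was meant.

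A second reply is that covariate choice belongs in the statistical analysis plan, which is not shown, and that an article condenses. That would answer a complaint about missing detail. Here a stated analysis is one that two countries cannot deliver, and a fuller plan could not make the indicators identifiable.

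A third is that the UK nations may be meant as countries. The references to Health Boards and to Welsh-language documents are compatible with that, but nothing says so. Step 4 shows that it would soften the result without rescuing it.

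A reader might also infer something stronger: that modelling clustering at hospital level only makes the standard error of the country coefficient too small, so that false positives would be frequent. The documents do not support this. It requires treating the UK and Queensland as random draws from a population of countries, an estimand the protocol does not state. It also requires a between-country variance and a Queensland share of the sample, neither of which the protocol gives. For a fixed contrast between these two places, a standard error that allows for hospital clustering is adequate, and the recommended model would keep it.

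**Conclusion.** The point holds for the country-level part of the sentence. With the UK and Australia as the only countries, no indicator that is constant within country can be separated from country, and no more than one can be fitted even if the country term is left out. This is algebra; it depends only on the number of countries, not on effect sizes or recruitment. The premise would change only if the UK nations were counted separately, and then at most four indicators could be fitted, saturating the between-country variation.

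The reach is narrow. The primary incidence estimate does not depend on this model. Hospital, patient, anaesthetic and obstetric factors, which are the substance of RQ3, remain open to estimation. A single country term is a legitimate adjustment and a legitimate description; it cannot be credited to a particular structure or process. If the Australian sites are all in Queensland, as the abstract says, it compares the UK with one Australian state. Severity is minor: a secondary analysis, with a fault of attribution and not of precision.

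**What to change.** In Inferential statistics, confine the indicators to the institutional ones and give country its own place, for example: *institutional structural and process indicators, with country (UK versus Queensland) as a single fixed effect*. Three consequences should be stated:

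- Hospital indicators are estimated adjusted for country, that is, from differences between hospitals within the same country.
- The country term is reported only as a descriptive UK–Queensland contrast, not as the effect of any national structure or process.
- The label for that term follows the sites that took part; UK versus Queensland is right unless other Australian states contributed.

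Showing the hospital-indicator results for UK sites alone is an optional sensitivity analysis.

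The cost is a change of wording and, if wanted, one extra model. What is given up is a claim about country-level structures that two countries cannot support.
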